### Sample size

Power size calculation was performed with GPower 3.1. Considering an anticipated effect size (*f*) of.25, an alpha set at 0.05, 2 groups, and a 0.95 statistical power, the total sample size required is *N* = 54. We, therefore, plan to enroll a total of 60 participants, which should guarantee a proper sample even in case of drop-outs.

### Recruitment

Healthcare workers will be informed about the possibility of participating in the study with oral communication and a formal email from the institutional study referent. They should confirm their intent to join the study by answering that email, and the referent will set an appointment for the screening interview, as described below.

### Eligibility criteria

The participants’ eligibility will be verified through a screening interview with the research psychologist, who will explain the training’s purpose and procedures and conduct an assessment to identify the participants who can enter the study. On this occasion, if the psychologist detects levels and symptoms of stress and/or anxiety of clinical interest, the participant will be sent to the Institutional Psychological Help Desk and excluded from the study.

The study inclusion criteria will be (1) being currently employed as a healthcare worker, (2) maximum age of 65, (3) absence of medical disorders (heart disease or blood pressure, neurological disorders, epilepsy), (4) absence of pharmacotherapy that could interfere with the measured data (psychoactive drugs, anti-hypertensive, anti-depressants), and (5) no significant visual impairment (all with normal visual acuity or corrected to normal).

### Allocation

During the interview, eligible participants who will meet the inclusion criteria described above will receive written information about the procedure and be asked to sign the consent form indicating their willingness to participate in the study. Participants will also be required to fill out baseline questionnaires accessible online. Only qualified individuals who provided informed consent will be randomly assigned to the experimental or control group in a 1:1 manner. Participants will then receive information regarding the allocation result.

### Randomization

The study coordinator will prepare the randomized sequence with a block randomization procedure using a true random number generator: www.randomizer.org. The randomized list will be created using a reasonably sized permuted block method, the block size of which will not be disclosed until the end of this trial to ensure concealment.

### Withdrawn criteria

Participants will be considered withdrawn if any of the following occurs: (1) participant chooses to withdraw from the study at any time, (2) intolerable adverse effects, (3) major violation of the study protocol, and (4) other circumstances that would endanger the health of the subject if he/she were to continue his/her participation in the trial. The date and reason for withdrawal will be documented in a paper-and-pencil case report form (CRF).

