### Strategies for monitoring and improving intervention protocol adherence

All participants will be invited to contact the research psychologist as needed. Participants in the experimental group will be provided with a log book to record technical problems, safety issues, and the date and time they used VR during the intervention. Besides, the research psychologist will monitor the intervention adherence using remote access to the online questionnaires dataset. Participants who will not have completed the pre- and post-training session scales on the scheduled dates will receive an email and a text message encouraging them to use VR. Furthermore, the psychologist will send an email and a text message to remind participants to complete the post-intervention and follow-up assessment, respectively, at the end and 1 month after the intervention. Participants in the experimental group will also be reminded to participate in the post-training session. The psychologist will contact via a phone call those who will not fill out online questionnaires at the scheduled times and individuals in the experimental group who will not attend the post-training session.

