#### Experimental group

Participants in the experimental group will receive the home-based VR intervention. Following a description of the protocol in detail:*Intake session (session 1):* after signing the informed consent and completing the baseline questionnaire accessible online (i.e., demographic, ad hoc questionnaire about the use of technological solutions and VR, ad hoc questionnaire on the level of exposure to COVID-19, FCOR, ad hoc questionnaire on stress and anxiety management, PSS-10, STAI-Y2, DASS-21, ad hoc questionnaire on knowledge of stress and anxiety), participants will receive from the research psychologist an explanation about the aims and methods of the home-based VR program. Participants will be asked for their involvement and availability during a week to allow in-home training. The psychologist will remind participants to perform the training three per week, with a distance of 2 days between one session and another. Then, individuals will receive information about the safety and hygiene procedures to prevent COVID-19 infection (see Table 3). The psychologist will give participants the Oculus Quest 2, a consumer-grade standalone VR system that consists of an HMD and two controllers. Individuals will wear the headset and receive a short 15-min training on using the VR system. In particular, they will try the tutorial content available on the Oculus Store. Furthermore, individuals will receive a link to complete the online questionnaires (i.e., STAI-Y1, VAS-A) before and after each session. They will be provided with a log book in which to record technical problems, safety issues, and the date and time they used VR during the intervention. Finally, the research psychologist will schedule the date of the post-training session.*Training sessions (sessions 2, 3, and 4):* they will consist of three home sessions of approximately 30 min each, conducted in a week with a distance of 2 days between one session and another. Participants will try for about 15 min one path of the virtual psychoeducational experience MIND-VR in each session (see Fig. 2). Subsequently, they will use for about 10 min the virtual relaxation content The Secret Garden. Individuals will be asked to complete online the VAS-A and the STAI-Y1 at the beginning and the end of each session.*Post-training session (session 5):* the research psychologist will meet participants for the post-intervention interview at the end of the training. On this occasion, participants will return the Oculus Quest 2, which will undergo specific procedures to avoid contamination by COVID-19. Participants will be asked to complete within 1 week after completion of the intervention the online questionnaires (i.e., PSS-10, STAI-Y2, DASS-21, ad hoc questionnaire on knowledge of stress and anxiety, SUS, SDM, NPS, ad hoc questionnaire on difficulties and adverse effects).*Follow-up session (session 6):* the PSS-10, STAI-Y2, DASS-21, and the ad hoc questionnaire on knowledge of stress and anxiety will be conducted after a 1-month follow-up.

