#### Control group

This group will undergo baseline, post-intervention, and follow-up assessments without undergoing any training during the 1-week intervention period.

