### Data analysis

Analysis of variance will be used to evaluate baseline characteristics of the two groups involved in the study, the overall significance of improvement across primary outcome measures, and drop-out versus maintainers. Categorical variables will be compared using Fisher or chi-square tests and continuous variables using *t*-test or Mann–Whitney tests, as appropriate. To assess the effectiveness of the intervention, groups will be compared with a 2 × 2 repeated measure mixed ANOVA for the pre- and post-primary outcome measures (factor Group X factor Time: pre and post). The analysis will be performed for the PSS, STAY-Y2, and DASS-21. A repeated-measures ANOVA (factor Group × factor Time: day of the week) will compare treatment effects within the 1-week intervention for the STAY-Y2 and the VAS-A. Tests of statistical significance and confidence intervals will be two-sided. A *p* < 0.05 will be considered statistically significant. Descriptive methods will be used to report the usability of the intervention for the secondary outcome intervention (i.e., SUS, SDM, NPS, ad hoc questionnaire on difficulties and adverse effects). Data analyses will be carried out through SPSS software.

Recordings from the post-intervention interviews will be transcribed. Two researchers will read the interview transcripts carefully several times to have a sense of the whole data, identifying emerging themes and categories [87]. A codebook will be created and modified until the final set of codes is obtained and reached to the data saturation point when there is no emergence of other new themes. Qualitative data analysis will be conducted using a thematic content analysis approach following a systematic process. Codes will be applied to the transcripts and converted into categories to represent the main themes arising from the data [88]. Triangulation of themes and concepts will be used to compare further and contrast the data from the different participating groups. Codes will be applied to the transcripts and converted into categories to represent the main themes arising from the data [88].

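### Counting an undefined major protocol violation as withdrawal from the trial can cause post-randomisation loss that falls mainly on the VR arm

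*Protocol article*

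**What the plan says.** The section Withdrawn criteria opens with "Participants will be considered withdrawn if any of the following occurs" and gives four grounds. They are the participant's own choice, "2) intolerable adverse effects", "3) major violation of the study protocol", and other circumstances that would endanger the participant's health. The first ground speaks of leaving the study and the fourth of continuing in the trial. The only stated consequence is "The date and reason for withdrawal will be documented in a paper-and-pencil case report form (CRF").

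The two arms have different duties. For the VR arm, the training sessions are set out thus: "they will consist of three home sessions of approximately 30 min each, conducted in a week with a distance of 2 days" between them. That arm also has scales before and after each session, a log book and a post-training meeting. For controls: "This group will undergo baseline, post-intervention, and follow-up assessments without undergoing any training during the 1-week intervention period".

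Under Data analysis, effectiveness is tested with a 2 × 2 "repeated measure mixed ANOVA for the pre- and post-primary outcome measures".

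Under the adherence section, VR participants who miss the session scales "will receive an email and a text message encouraging them to use VR". People who miss the scheduled questionnaires are phoned. Under Secondary outcome measure, sessions completed, assessments attended and drop-outs are collected as adherence data.

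**The concern.** A protocol violation during the training week happens after randomisation. It may be related to how the participant is doing, for example when workload, stress or symptoms get in the way of the sessions. If such a person counts as having left the trial, no post-intervention score would be expected from them, and a later analysis plan cannot recover a score that was never collected.

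The VR arm has a regimen with several places to go wrong. The control arm has only questionnaires to complete. Losses under this ground would therefore fall mainly on one side, and the people left in the VR arm would no longer be the group that randomisation created. What is at stake is the validity of the between-group comparison on the primary outcomes, more than its precision.

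**Working it through.** **1. The plan's own sample size.** Inputs from Sample size: f = 0.25, alpha 0.05, 2 groups, power 0.95, required N = 54, enrolled 60. Assumed: 2 measurements and a pre-post correlation ρ = 0.5, which the article does not state (it is the software default). For the group-by-time interaction:

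- λ = f² × N × m / (1 − ρ) = 0.0625 × 54 × 2 / 0.5 = 13.5, with 1 and 52 degrees of freedom. Power is 0.9501, so 54 reproduces.
- With all 60 kept, λ = 0.0625 × 60 × 2 / 0.5 = 15 and power is 0.968.

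This test equals a t-test on change. With ρ = 0.5 the SD of change is √(2 × 0.5) = 1 score SD. With 27 per arm the squared noncentrality is D² / (2/27) = 13.5 × D², so λ = 13.5 corresponds to D = 1.0 SD. That gives a scale for the biases below.

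**2. What the sections imply together.**

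- Withdrawn criteria: a major violation means withdrawn, and the surrounding wording equates withdrawn with out of the trial.
- Experimental group and Control group: one arm has training to violate, the other has none.
- Experimental group, post-training session: the post questionnaires are timed from completing the intervention. Someone who does not complete has no clear anchor in that text, although Table 2 lists week 1.
- Data analysis: the test needs a pre and a post score for each person.
- Allocation: participants are told their group. The article does not say who decides that a violation is major, but the psychologist who monitors adherence also hands out the headsets and so knows the arm.

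**3. Illustration of the possible bias.** Assumptions: no true effect, 30 per arm, no controls removed, a share q of the VR arm removed (the least adherent), and correlation r between adherence and improvement. In large samples the retained VR mean shifts by r × φ(z_q) / (1 − q), where z_q cuts off the lowest share q:

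- q = 10%: 0.1755 / 0.9 = 0.195, times r = 0.059 (r = 0.3) or 0.098 (r = 0.5)
- q = 20%: 0.2800 / 0.8 = 0.350, times r = 0.105 or 0.175
- q = 30%: 0.3477 / 0.7 = 0.497, times r = 0.149 or 0.248

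Simulation at the trial's size (40,000 trials per cell, two-sided t-test on change) agrees:

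| VR participants removed | r = 0: type I error | r = 0.3: bias, type I error | r = 0.5: bias, type I error |
|---|---|---|---|
| 3 of 30 (10%) | 4.9% | 0.06 SD, 5.6% | 0.10 SD, 6.7% |
| 6 of 30 (20%) | 5.2% | 0.10 SD, 6.5% | 0.17 SD, 9.9% |
| 9 of 30 (30%) | 4.9% | 0.15 SD, 8.0% | 0.24 SD, 14.0% |

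The simulation error at 5% is √(0.05 × 0.95 / 40,000) = 0.1 percentage points, so the r = 0 column is 5% within noise. A repeat with 200,000 trials per cell for r = 0.3 and 0.5 gave the same error rates to within 0.2 points. A negative r would give biases of the same size against VR, by symmetry.

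**4. Power.** With D = 1.0 SD, removing 3, 6 or 9 VR participants leaves power of 0.959, 0.948 or 0.931. The loss of precision is small; the issue is bias.

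**The case against.** The tempting stronger reading is that the ANOVA will compare adherent VR users with all controls. The documents do not support it, for three reasons.

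- Nothing says that withdrawn people are excluded from the analysis. The one stated consequence is a CRF entry, and no per-protocol or completer set is named.
- Nothing says that missed sessions are major violations. The stated response to them is a reminder, and session completion is recorded as adherence data.
- Controls can be lost too, by choice or by missing assessments. A violation could also be arm-neutral, such as an ineligibility found late.

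The magnitude is open to challenge as well. The only anchor for drop-out is the margin of 60 − 54 = 6 people for both arms together, so losing 9 from one arm through this ground alone would exceed it. The direction is not settled either. If people with high baseline stress are the ones removed, regression to the mean could make the bias run against VR.

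Finally, analysis sets and missing-data methods may lie in an analysis plan, and the definition of a major violation in a fuller protocol. Their absence from an article is not a fault, and the article does plan to compare drop-outs with those who stay.

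All of this stands, and it limits the point to a risk. It does not remove the point. The article states a withdrawal rule whose wording ends trial participation. Imputation could fill a missing post score but not replace the observed one. The reminders and calls are not said to continue for someone already withdrawn.

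**Conclusion.** The rule as written can produce post-randomisation loss that falls mainly on the VR arm, and that loss can bias the primary comparison. This rests on the protocol's own wording and on the different duties of the two arms, and not on a missing analysis set.

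Size and direction are not fixed by the document. There is no inflation if removal is unrelated to improvement. Under the assumed removal of 10–30% of the VR arm and correlations of 0.3–0.5, the type I error is about 5.6–14% and the spurious difference 0.06–0.24 SD, against a planned effect of 1.0 SD on the same scale (at ρ = 0.5). A reader might infer that the result will be biased in favour of VR; that direction comes from the assumed sign of the correlation. The sample size of 54 is not affected.

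**What to change.** - Do not use a protocol violation as a ground for ending trial assessments. Record it with the adherence data that the protocol already collects.
- State that stopping VR, for whatever reason, does not end assessment. The PSS-10, STAI-Y2, DASS-21 and knowledge questionnaire are still requested at the post-intervention and follow-up time points of Table 2, unless the participant withdraws consent.
- State that all participants are analysed in the arm to which they were randomised.
- Leave the clinical reasons for stopping VR as they are. The change concerns data collection and analysis only.

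The cost is protocol wording and slightly more follow-up effort, since the questionnaires are online and reminders and calls are already planned. The estimated effect may come out smaller, because people who did not follow the training stay in the comparison.

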### Strategies for monitoring and improving intervention protocol adherence

All participants will be invited to contact the research psychologist as needed. Participants in the experimental group will be provided with a log book to record technical problems, safety issues, and the date and time they used VR during the intervention. Besides, the research psychologist will monitor the intervention adherence using remote access to the online questionnaires dataset. Participants who will not have completed the pre- and post-training session scales on the scheduled dates will receive an email and a text message encouraging them to use VR. Furthermore, the psychologist will send an email and a text message to remind participants to complete the post-intervention and follow-up assessment, respectively, at the end and 1 month after the intervention. Participants in the experimental group will also be reminded to participate in the post-training session. The psychologist will contact via a phone call those who will not fill out online questionnaires at the scheduled times and individuals in the experimental group who will not attend the post-training session.

### Participant timeline

The trial period is shown in the consolidated standards of reporting trials diagram [68] (Fig. 1) and Standard Protocol Items: Recommendations for Interventional Trials template [69] (Table 2).

**Fig. 1 Fig1:**
[figure not shown]
Flow chart of the study design

**Table 2 Tab2:** Assessment schedule

	**Study period**					
	**Enrolment**	**Baseline**	**Allocation**	**Intervention**	**Post-intervention**	**Follow-up**
**Timepoint (weeks)**	** − 1**	**0**	**0**	**0**	**1**	**5**
Enrolment:						
Eligibility screen	X					
Informed consent	X					
Allocation			X			
Interventions						
Experimental group				↔		
Control group				↔		
Assessments:						
Demographics		X				
Use of technological solutions and VR		X				
Level of exposure to COVID-19		X				
FCOR		X				
Stress and anxiety management		X				
PSS-10		X			X	X
STAI-Y2		X			X	X
DASS-21		X			X	X
Knowledge of stress and anxiety		X			X	X
STAI-Y1				X		
VAS-A				X		
SUS					X	
SDM					X	
NPS					X	
Difficulties and adverse effects					X	
Interview					X	

*FCOR* Fear of Coronavirus, *PSS-10* Perceived Stress Scale, *STAI-Y2* State-Trait Anxiety Inventory Form Y-2, *DASS-21* The Depression, Anxiety and Stress Scale-21 Items, *STAI-Y1* State-Trait Anxiety Inventory Form Y-1, *VAS-A* Visual Analogue Scale for Anxiety, *SUS* System Usability Score, *SDM* Subjective Difficulty Measure, *NPS* Net Promoter Score

### Protocol

Participants will be randomly assigned to one of the two following conditions:Experimental groupControl group

#### Experimental group

Participants in the experimental group will receive the home-based VR intervention. Following a description of the protocol in detail:*Intake session (session 1):* after signing the informed consent and completing the baseline questionnaire accessible online (i.e., demographic, ad hoc questionnaire about the use of technological solutions and VR, ad hoc questionnaire on the level of exposure to COVID-19, FCOR, ad hoc questionnaire on stress and anxiety management, PSS-10, STAI-Y2, DASS-21, ad hoc questionnaire on knowledge of stress and anxiety), participants will receive from the research psychologist an explanation about the aims and methods of the home-based VR program. Participants will be asked for their involvement and availability during a week to allow in-home training. The psychologist will remind participants to perform the training three per week, with a distance of 2 days between one session and another. Then, individuals will receive information about the safety and hygiene procedures to prevent COVID-19 infection (see Table 3). The psychologist will give participants the Oculus Quest 2, a consumer-grade standalone VR system that consists of an HMD and two controllers. Individuals will wear the headset and receive a short 15-min training on using the VR system. In particular, they will try the tutorial content available on the Oculus Store. Furthermore, individuals will receive a link to complete the online questionnaires (i.e., STAI-Y1, VAS-A) before and after each session. They will be provided with a log book in which to record technical problems, safety issues, and the date and time they used VR during the intervention. Finally, the research psychologist will schedule the date of the post-training session.*Training sessions (sessions 2, 3, and 4):* they will consist of three home sessions of approximately 30 min each, conducted in a week with a distance of 2 days between one session and another. Participants will try for about 15 min one path of the virtual psychoeducational experience MIND-VR in each session (see Fig. 2). Subsequently, they will use for about 10 min the virtual relaxation content The Secret Garden. Individuals will be asked to complete online the VAS-A and the STAI-Y1 at the beginning and the end of each session.*Post-training session (session 5):* the research psychologist will meet participants for the post-intervention interview at the end of the training. On this occasion, participants will return the Oculus Quest 2, which will undergo specific procedures to avoid contamination by COVID-19. Participants will be asked to complete within 1 week after completion of the intervention the online questionnaires (i.e., PSS-10, STAI-Y2, DASS-21, ad hoc questionnaire on knowledge of stress and anxiety, SUS, SDM, NPS, ad hoc questionnaire on difficulties and adverse effects).*Follow-up session (session 6):* the PSS-10, STAI-Y2, DASS-21, and the ad hoc questionnaire on knowledge of stress and anxiety will be conducted after a 1-month follow-up.

**Table 3 Tab3:** Safety and hygiene protocol to prevent COVID-19 infection during the intake and the post-training sessions

Safety and hygiene protocol
***Instruct the participant on the safety and hygiene procedure*** •Inform the participant on the importance of the safety and hygiene procedure •During the intake and post-training session, participants will be asked to follow specific precautions described below •Participants with cold-like symptoms will be asked not to go to the experiment and to notify the experimenter
***Follow the following precautions during the intake session*** •To ensure the safety procedures for the prevention of COVID-19 infection, the session will be conducted in a clean and well-ventilated room inside the hospital •Before entering the room, both the experimenter and the participants will have to wash their hands with an alcohol-based disinfectant (at least 70%) •Tell the user to keep at least 1.5 m from the experimenter •The participant will take the headset placed on a table placed about 3 m away from the experimenter and will be explained how to wear it independently and how to use it
***Disinfect the headset after the post-training session*** •As soon as the session is finished, the experimenter will use a detergent with at least 70% alcohol to decontaminate the headset •The cleanable, waterproof face part, keys areas of the headset (i.e., top and bottom, the headbands, buttons), and controllers will be disinfected and allowed to dry on a clean surface •At the end of the procedure, the experimenter will have to disinfect his/her hands again

